#### Strategies to improve adherence to interventions {11c}

Participants will be informed about the indication for arthroscopy irrespective of study participation. Close examination and clinical testing will reduce the number of patients who will have to be excluded due to an inability to perform the required radio-ulnar motion.

#### Relevant concomitant care permitted or prohibited during the trial {11d}

Not applicable to this diagnostic study.

#### Provisions for post-trial care {30}

As a purely observational study, participants will receive standard imaging/diagnostics and care during the trial. No study specific radiation exposure, clinical examinations, therapies, or follow-up exams will be conducted. Patients will be insured through the hospital’s liability insurance.

#### Outcomes {12}

Measurements on 4D CT reconstructions and cineradiography 1–7 days preoperatively will be used as index tests [Table 1] to calculate diagnostic accuracies of both methods for detecting instable SLL tears as stipulated by the reference test arthroscopy.

**Table 1 Tab1:** Radiological classification of stability

Stability	SLD_**min**_ (mm)	SLD_**max**_ (mm)	SL °	RL °
stable	< 3	< 3	< 60	> −15
instable	< 3 or > 3	> 3	> 60	> −15 or < − 15

SL distance = *SLD*, radiolunate= *RL*, scapholunate SL angle)

Binary classification of therapeutic indication to conservative therapy vs surgery determined by arthroscopy will be used as reference test to classify SLL injuries [Table 2].

**Table 2 Tab2:** Arthroscopic classification of stability

Stability	Stadium (Geissler/ EWAS)	Anatomical Correlation	Arthroscopic test
stable	I	elongation	Microhook cannot be advanced into the joint
	II	rupture of membranous portion of SLL	Microhook can be advanced into the joint but joint is not widened
unstable	IIIA	II + rupture of palmar portion of SLL	Joint widens on the palmar side during manipulation with microhook
	IIIB	II + rupture of dorsal portion of SLL	Joint widens on the dorsal side during manipulation with microhook
	IIIC	II + rupture of palmar and dorsal portion	Joint widens on both palmar side during manipulation with microhook but closes after manipulation
	IV	IIIC + widening of SL joint	Joint can be passed by arthroscope
	V	IV + tilting of carpalia	widening of SL joint with pathological plain radiographs

Validity will be described by sensitivity and specificity of a diagnostic test [18]. Both index tests, 4D CT and cineradiography, will be opposed to the reference test arthroscopy. Optimal cut-off points are determined using area under the receiver operating characteristic (AUC-ROC) curves [19].

Effective skin dose measurements will be enabled using thermoluminescent dosimeters (TLD) during 4D CT at defined regions of interest (head, affected hand and shoulder).

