#### Intervention description {11a}

All patients with a typical trauma mechanism and wrist pain presenting through the ambulance or emergency room will be screened for eligibility. Patients will be examined and will receive radiographs of the wrist in two planes routinely. In cases of suspected SLL tear and indication for arthroscopy, patients will be informed about the possibility of study participation by the attending hand surgeon.

According to the inclusion and exclusion criteria 40 participants will be enrolled consecutively after written consent.

4D CT scans of the injured wrist will be performed preoperatively and analyzed by two specialized radiologists. Coronal reconstructions will be used to measure the maximum and minimum scapholunate distance (SLD). On sagittal reconstructions the scapholunate (SL) and radiolunate (RL) angle will be determined to classify SLL tears as stable or unstable.

The patients will not be exposed to radiation for research purposes. Arthroscopy will be performed as the diagnostic gold standard within the same week to classify the type of SLL tear according to the European Wrist Arthroscopy Society (EWAS) and Geissler [16, 17]. Primary reconstruction and temporary arthrodesis will be performed when necessary, but the surgical therapy will not be part of the study.

We will conduct an additional screening of historical patient records for eligibility, inclusion, and exclusion criteria. These historical patients with a typical trauma and wrist pain were also examined clinically and received radiographs of the wrist in two planes routinely. In cases of suspected SLL tear, cineradiography was performed before arthroscopy. After written consent 80 consecutive patient who were diagnosed through cineradiography before arthroscopy will be enrolled. Measurement of minimum and maximum SLD on anterior-posterior projections, of SL angle, and RL angle on lateral projections will be measured to classify SLL tears as stable or unstable and to compare these results to the findings of arthroscopy. The diagnostic accuracy of cineradiography will serve as a comparison for the sensitivity and specificity of 4D CT in suspected SLL tears.

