**Epidemiology:**		
Gender	Male	Female
Side of injury	Right	Left
Handedness	Right	Left
Date of injury		
Age at the day of injury		
**Clinical examination:** Date		
Watson-Test	Positive	Negative
Localized pain during compression of dorsal SLL	Yes	No
**Arthroscopy:** Date		
Age at the day of arthroscopy		
EWAS/Geissler Stadium		
Stability	Stable	Unstable

4D CTs will be acquired using a dual-source scanner with 2 × 192 rows and a detector width of 6 cm (Somatom Force, Siemens, Germany). Patients will be placed in prone position with the injured wrist reaching into the gantry (“superman position”). Patients will be instructed to perform a radio-ulnar movement during an 8 s scan cycle. Forearms will only be lightly fixated with a tape as a reminder for the patients to reside to wrist movements only. Postprocessing will be performed using a designated software (Syngo.Via Version VB10B-VB30A, Siemens, Germany). Reconstructions include dynamic 5 mm and 1 mm coronal reconstructions as well as static coronal and sagittal reconstructions of 2 mm. Table 5 summarizes the acquisition parameters of 4D CT.

**Table 5 Tab5:** Parameters of 4D CT

Tube voltage (kV)	80
Milliamperage (mAs)	70
Section thickness (mm)	1
Length (mm)	56
Number of slices	1254
Collimation	384 × 1 mm
Reconstruction matrix	Soft-tissue and bone kernel
Image reconstruction	512 × 512

Radiologists will document results of 4D CT in a standardized manner to describe stability of the SLL ([20], Table 6). SLD will be measured in the center of the SL joint during radio-ulnar motion at minimum and maximum width [21, 22]. Carpal angles will be measured on sagittal reconstructions according to the radial axis [23, 24].

**Table 6 Tab6:** Radiological Report

Patient-ID:		
**Parameter:** Date		
Modality	4D CT	Cineradiography
Date of imaging		
SLD_min_		
SLD_max_		
SL angle		
RL angle		
**Stability**	Stable	Unstable

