### Statistical methods

#### Statistical methods for primary and secondary outcomes {20a}

All statistical analyses will be conducted in an exploratory, hypotheses-generating fashion. For both index tests AUCs as well as sensitivity and specificity with 95% confidence intervals will be calculated. Descriptive statistics dependent on scale and distribution will be reported for all parameters.

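### Table 1, the index-test rule for both 4D CT and cineradiography, leaves many combinations of measurements without a class, so the binary call depends on unstated reader choices

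*Protocol article*

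**What the plan says.** Outcomes {12} of the protocol article makes Table 1 the classification rule for both modalities: the measurements "will be used as index tests [Table 1] to calculate diagnostic accuracies of both methods for detecting instable SLL tears". The columns of the table are SLDmin (mm), SLDmax (mm), SL angle and RL angle, and it has two rows:

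- "stable < 3 < 3 < 60 > −15"
- "instable < 3 or > 3 > 3 > 60 > −15 or < − 15"

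Intervention description {11a} adds that "On sagittal reconstructions the scapholunate (SL) and radiolunate (RL) angle will be determined to classify SLL tears as stable or unstable", and gives the same purpose to the cineradiography measurements. Neither section says how the four columns combine or which one prevails when they disagree.

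The radiological report (Table 6, under Plans for assessment and collection of outcomes {18a}) records all four measurements and then one two-option field: "Stability Stable Unstable". It offers no indeterminate category.

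The analysis section {20a} states: "For both index tests AUCs as well as sensitivity and specificity with 95% confidence intervals will be calculated". Outcomes {12} also says: "Optimal cut-off points are determined using area under the receiver operating characteristic (AUC-ROC) curves". The relation of those cut-offs to the thresholds in Table 1 is not stated. Section {20b} plans a kappa statistic between two radiologists for each modality.

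**The concern.** A binary index test needs a rule that puts every wrist in exactly one class. Read as printed, the stable row requires all four measurements to be normal. The instable row requires SLDmax and SL both to be abnormal, and leaves SLDmin and RL free. Wrists between these two descriptions have no class, yet the reader must tick one.

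The consequence falls on the primary objectives, which are the accuracy of 4D CT and its comparison with cineradiography. If one reader calls a wide gap with a normal angle unstable and another calls it stable, sensitivity and specificity shift with the reader. Kappa on the stable/unstable call then partly measures disagreement about the rule and not about the images. If the convention differs between 4D CT and cineradiography, the comparison of modalities is affected as well.

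**Working it through.** **1. Coverage of Table 1.** The inputs are the two rows of Table 1. Each measurement is placed on one side of its cut-off: 3 mm for SLDmin and SLDmax, 60° for SL, −15° for RL. SLDmin cannot exceed SLDmax, so the pair (SLDmin, SLDmax) has 3 feasible states. The number of patterns is 3 × 2 × 2 = 12.

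| Pattern | Count | Row matched |
|---|---|---|
| SLDmax < 3, SL < 60, RL > −15 (hence SLDmin < 3) | 1 | stable |
| SLDmax > 3, SL > 60, any SLDmin, any RL | 4 | instable |
| SLDmax > 3, SL < 60, any SLDmin, any RL | 4 | neither |
| SLDmax < 3, SL > 60, any RL | 2 | neither |
| SLDmax < 3, SL < 60, RL < −15 | 1 | neither |

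Totals: 1 stable, 4 instable, 7 neither, none both. All inequalities are strict, so SLDmax of exactly 3 mm or SL of exactly 60° also matches neither row.

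**2. Can another reading close the gap?**

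- *Join the whole instable row by OR.* The SLDmin and RL cells accept either side of the cut-off, so virtually every wrist would be instable, including those that meet the stable row.
- *Use OR for SLDmax and SL only.* This assigns 10 patterns to instable, but the pattern with RL as the only abnormality still has no class.
- *Treat everything not instable as stable.* This contradicts the stable row, which requires every measurement to be normal.

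**3. Size (illustration).** The documents give neither the accuracy of single measurements nor the frequency of discordance. Assumptions:

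- 20 instable and 20 stable wrists, out of the planned 40.
- SLDmax > 3 has sensitivity 0.85 and specificity 0.90.
- SL > 60 has sensitivity 0.65 and specificity 0.85.

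*Conditional independence*

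- Discordant among instable: 0.85 × 0.35 + 0.15 × 0.65 = 0.395.
- Discordant among stable: 0.10 × 0.85 + 0.90 × 0.15 = 0.22.
- Total: 20 × 0.395 + 20 × 0.22 = 12.3 of 40.
- Both abnormal required: sensitivity 0.85 × 0.65 = 0.5525; specificity 1 − 0.10 × 0.15 = 0.985.
- Either abnormal suffices: sensitivity 1 − 0.15 × 0.35 = 0.9475; specificity 0.90 × 0.85 = 0.765.

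*Maximal positive dependence*

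- Discordant among instable: 0.85 − 0.65 = 0.20.
- Discordant among stable: 0.15 − 0.10 = 0.05.
- Total: 20 × 0.20 + 20 × 0.05 = 5 of 40.
- Both abnormal required: sensitivity 0.65; specificity 1 − 0.10 = 0.90.
- Either abnormal suffices: sensitivity 0.85; specificity 1 − 0.15 = 0.85.

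| Dependence | Discordant of 40 | Both abnormal (sens/spec) | Either abnormal (sens/spec) |
|---|---|---|---|
| Maximal positive | 5 | 65% / 90% | 85% / 85% |
| Independent | about 12 | 55% / 98.5% | 95% / 76.5% |

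The counts move with the assumed accuracies. If both measures have sensitivity and specificity p and are conditionally independent, the discordant share is 2p(1 − p). At p = 0.90, 0.80 and 0.70 this is 18%, 32% and 42%, or about 7, 13 and 17 of 40.

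**The case against.** **Figures can still be produced.** A reader might infer that sensitivity and specificity cannot be computed at all. The documents do not support that. Table 6 forces a tick, so every wrist gets a cell in the two-by-two table, and the AUC of a single measurement does not need Table 1. This objection stands. The defect is that the binary call cannot be reproduced from Table 1 for discordant wrists.

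**A static angle would limit a dynamic test.** It is also tempting to argue that the plan defeats its own purpose. Sagittal images, on which the angles are read, are listed only among the "static coronal and sagittal reconstructions of 2 mm". If both SLDmax and SL must be abnormal, sensitivity cannot exceed that of the SL angle alone. But this follows only if that combination is adopted and the 60° cut-off is kept. The protocol states no rule for combining the columns, and it plans ROC-derived cut-offs, so the limit is conditional and not a feature of the plan.

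**The detail may be elsewhere.** Section {18a} cites a source for standardised reporting, and a fuller protocol or analysis plan may exist. The assignment of values exactly on a cut-off could reasonably be left there. The main gap is different: the article prints the rule and names it as the index test, and the printed rule fails.

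**The study is exploratory, and care does not depend on the 4D CT result.** Both are true and limit the consequences. Accuracy is nevertheless the primary objective, and the Discussion expects reliable diagnostic parameters.

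**The size is uncertain.** Seven of 12 counts patterns and says nothing about how many patients fall in them. Independence is doubtful for two measures of the same joint, which is why the maximal-dependence case is shown beside it.

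**Conclusion.** The point holds in this form: the index-test rule in Table 1 is not exhaustive, with 7 of 12 feasible patterns and exact values on the SLDmax or SL cut-off fitting neither row, while the report form demands a binary answer. That part rests on the printed table alone. Sensitivity, specificity and kappa for the binary call therefore depend on choices that the document does not state.

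The practical size is unknown. Under the accuracies assumed above and a 20/20 split, about 5 to 12 of 40 wrists are discordant. The choice between requiring both and accepting either abnormality moves sensitivity by 20 points (65% to 85%) under maximal dependence and by about 40 points (55% to 95%) under independence. Specificity falls by 5 points (90% to 85%) and 22 points (98.5% to 76.5%) respectively. These figures show that the rule can matter; they do not predict the trial's result.

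**What to change.** Before analysis, the investigators should:

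1. Replace Table 1 by one exhaustive, mutually exclusive rule of their choice. It should state how SLDmax, SL and RL combine and where values on a threshold go. The documents do not favour one combination over another. For example, calling every wrist that is not fully normal unstable would make an isolated RL below −15° decisive, although the instable row leaves RL free.
2. State whether the primary sensitivity and specificity use this rule or the ROC-derived cut-offs.
3. Derive the stable/unstable call by program from each reader's recorded measurements, identically for 4D CT and cineradiography.
4. Report the main alternative combination (both abnormal versus any abnormal) as a sensitivity analysis.

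The cost is protocol wording and one derived variable. No new data are needed, since all four measurements are already on Table 6.

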### Objectives {7}

Primary objectives:
Analysis of diagnostic accuracy of 4D CT for the differentiation between stable and instable SLL tears preoperatively.Comparison of diagnostic accuracies of 4D CT and cineradiography.

*Secondary objectives:*
Can 4D CT scans of the wrist detect secondary injuries as opposed to radiography?How do the stages of scapholunate dissociation correlate with the time interval between diagnostics and trauma?Are measured effective radiation skin doses in-vivo and calculated skin doses during 4D CT similar?Which diagnostic algorithm can be proposed for suspected SLL tears?

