#### Sample size {14}

The study will be conducted and analyzed in an exploratory fashion. Therefore, formal sample size calculations are deferred by the investigators. Instead, yearly patient numbers were estimated, and the number of participants was adapted to a two-year study design which results in a recruiting target of 40 patients used for estimation of diagnostic accuracy of 4D CT. The comparative historical cohort used for estimation of diagnostic accuracy of cineradiography should consist of 80 patients to account for a probably greater extent of heterogeneity in the retrospective data due to the fact that these were collected by different clinicians who were not instructed on data collection specifically for this trial.

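### The protocol gives both fixed Table 1 thresholds and ROC-derived cut-offs without saying which yields the reported sensitivity and specificity; if the ROC-derived ones do, both are biased upward

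*Protocol article*

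**What the plan says.** The Outcomes section {12} of the protocol article gives two routes to a positive index test.

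- The fixed route: "Measurements on 4D CT reconstructions and cineradiography 1–7 days preoperatively will be used as index tests [Table 1] to calculate diagnostic accuracies of both methods". Table 1 sets the limits at 3 mm for the scapholunate distances, 60° for the scapholunate angle and −15° for the radiolunate angle.
- The data-derived route, after Table 2 in the same section: "Optimal cut-off points are determined using area under the receiver operating characteristic (AUC-ROC) curves [19".

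The statistical methods section {20a} then says: "For both index tests AUCs as well as sensitivity and specificity with 95% confidence intervals will be calculated". It does not name the cut-offs at which sensitivity and specificity are taken.

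The sample size section {14} describes the data: a "recruiting target of 40 patients used for estimation of diagnostic accuracy of 4D CT", and "The comparative historical cohort used for estimation of diagnostic accuracy of cineradiography should consist of 80 patients". No separate validation set is described. One of the two primary objectives {7} is "Comparison of diagnostic accuracies of 4D CT and cineradiography". The work is declared exploratory: "All statistical analyses will be conducted in an exploratory, hypotheses-generating fashion".

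**The concern.** Sensitivity and specificity depend on the rule that calls a wrist instable. Here two rules stand in one section, and the reader cannot tell which one the main results will follow.

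The choice matters because the rules behave differently. Table 1 is fixed before the data are seen. A ROC-derived cut-off is the one that best separates these particular patients according to arthroscopy. Evaluating it on the same patients counts part of their chance variation as accuracy. It would also replace the stable/unstable call that radiologists record in Table 6, blind to arthroscopy, with a rule fitted to arthroscopy.

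Both primary objectives rest on these figures. The bias also shrinks as the sample grows, and the two cohorts differ in size, so it need not cancel when the tests are compared.

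**Working it through.** **Plan's own figure.** There is none to reproduce. The protocol states no expected accuracy, and on sample size it says "Therefore, formal sample size calculations are deferred by the investigators". The 40 patients come from feasibility: about 30 arthroscopies a year × 2 years = 60, of which 40 is 67%.

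**Inputs from the protocol.** N = 40 for 4D CT and N = 80 for cineradiography, with the cut-off chosen and evaluated in the same cohort.

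**Assumptions not in the protocol.** One normally distributed marker with equal variance in both classes; cut-off at the maximum Youden index, J = sensitivity + specificity − 1; true AUC 0.70 to 0.95; 30%, 50% or 70% instable.

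**Method.** The separation of the class means is d = √2 × Φ⁻¹(AUC). In each of 4,000 simulated cohorts per setting, the cut-off c maximising J was found. True sensitivity at c is 1 − Φ(c − d) and true specificity is Φ(c). Bias is the mean of apparent minus true.

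**Result at 50% instable:**

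| AUC | N=40: sens / spec / sum | N=80: sens / spec / sum | Difference in sum |
|---|---|---|---|
| 0.70 | 0.076 / 0.073 / 0.149 | 0.053 / 0.052 / 0.105 | 0.044 |
| 0.80 | 0.068 / 0.066 / 0.133 | 0.047 / 0.045 / 0.092 | 0.041 |
| 0.90 | 0.056 / 0.054 / 0.110 | 0.037 / 0.037 / 0.074 | 0.036 |
| 0.95 | 0.048 / 0.045 / 0.093 | 0.032 / 0.032 / 0.064 | 0.029 |

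(Sums are rounded separately.)

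**Uneven split.** The smaller class carries more of the bias. At AUC 0.70 and N = 40, sensitivity is inflated by 0.116 with 30% instable, and specificity by 0.117 with 70% instable.

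**All settings, 30% to 70% instable.** The bias in the sum is 0.093 to 0.168 at N = 40 and 0.064 to 0.119 at N = 80. With AUC and prevalence equal in both cohorts, the ratio is 1.41 to 1.48 and the gap 0.03 to 0.05.

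**Control.** With one prespecified cut-off, the mean bias in the sum is −0.004 to +0.003 at both sizes, which is zero within simulation error.

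**Does the tilt survive unequal cohorts?** Bias in the sum, 4D CT (N = 40) against cineradiography (N = 80):

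- 50% instable in both, AUC 0.90 against 0.80: 0.112 against 0.089
- 50% instable in both, AUC 0.95 against 0.80: 0.092 against 0.090, no tilt
- 50% instable in both, AUC 0.95 against 0.70: 0.092 against 0.106, reversed
- AUC 0.85 in both, 50% against 20% instable: 0.124 against 0.111
- AUC 0.85 in both, 50% against 10% instable: 0.124 against 0.156, reversed

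**Tilt against sampling error.** Take AUC 0.85, 50% instable and a fixed cut-off at d/2. Then d = 1.414 × 1.036 = 1.466, and sensitivity = specificity = Φ(0.733) = 0.768. The variance of J is 2 × 0.768 × 0.232 / 20 = 0.0178 at N = 40 and 2 × 0.768 × 0.232 / 40 = 0.0089 at N = 80. The 95% half-width for the difference is 1.96 × √(0.0178 + 0.0089) = 0.32.

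**The case against.** The strongest reply is that the plan already settles the matter. The Outcomes section links accuracy directly to Table 1, the intervention description {11a} has the measurements taken in order to classify tears, and Table 6 records a binary result. On that reading the ROC cut-offs merely add a description of the continuous measurements, and the study is exploratory, with no hypothesis test or accuracy target at stake.

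Much of this stands. A reader might infer that the reported accuracy will be optimistic. The documents do not support that, because they leave the choice of rule open and Table 1 may well be what is meant. A reader might also infer that the cut-off search necessarily favours 4D CT. That rests on similar AUC and prevalence in the two cohorts, which the protocol does not give, and the tilt is small beside the sampling error of the comparison. Nor is there ground for adding bias from picking the best of the four measurements, since no section plans such a selection. The AUC of a parameter named in advance is not inflated by choosing a cut-off.

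The cut-off criterion and the interval method can properly be left to an analysis plan. Their absence is not the point here, and no interval method is named that could be called wrong.

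What does not stand is that the exploratory label resolves the ambiguity. It weakens the claims made from an estimate but does not remove bias from it, and the Discussion expects reliable diagnostic parameters for 4D CT. The ROC rule is stated text in the same section as Table 1, and nothing ranks one above the other.

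**Conclusion.** The point holds as a conditional one. The protocol gives two definitions of a positive test and does not say which yields sensitivity and specificity for the primary objectives.

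If the ROC-derived cut-offs are used uncorrected, both measures are biased upward: about 5 to 8 points each at 40 patients and 3 to 5 points each at 80 with an even split, and up to about 12 points in the smaller class at 40 patients with a 30/70 split. Confidence intervals that ignore the cut-off search would then be centred on inflated values. The effect on the comparison would be about 0.03 to 0.05 in sensitivity plus specificity in favour of 4D CT if the cohorts have similar AUC and prevalence. It vanishes or reverses if 4D CT discriminates much better or if the historical split is very uneven. If Table 1 is used, none of this arises.

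The sizes depend on the binormal model, the Youden criterion and the assumed AUC and prevalence. The ambiguity itself, and the upward direction of the bias within each cohort, do not depend on those particular values.

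**What to change.** State in the Outcomes and statistical methods sections that primary sensitivity and specificity, and the comparison with cineradiography, use only the prespecified Table 1 classification.

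For that rule to be usable, the investigators must say how patterns that fit neither row are classified, for example a maximum distance above 3 mm with a scapholunate angle below 60°. This should be settled before index and reference results are combined. The timing allows it, because the statistician receives the two departments' data only once collection is complete.

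Label ROC-derived cut-offs exploratory and name the selection criterion, for instance the Youden index. Report their accuracy only with bootstrap or cross-validated optimism correction, and with intervals that repeat the cut-off search in each resample.

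The cost is a few sentences and a short script. No extra patients or imaging are needed. The exploratory figures will look less favourable.
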